# Promotion of the mind through exercise (PROMoTE): a proof-of-concept randomized controlled trial of aerobic exercise training in older adults with vascular cognitive impairment

**DOI:** 10.1186/1471-2377-10-14

**Published:** 2010-02-17

## Abstract

**Background:**

Sub-cortical vascular ischaemia is the second most common etiology contributing to cognitive impairment in older adults, and is frequently under-diagnosed and under-treated. Although evidence is mounting that exercise has benefits for cognitive function among seniors, very few randomized controlled trials of exercise have been conducted in populations at high-risk for progression to dementia. Aerobic-based exercise training may be of specific benefit in delaying the progression of cognitive decline among seniors with vascular cognitive impairment by reducing key vascular risk factors associated with metabolic syndrome. Thus, we aim to carry out a proof-of-concept single-blinded randomized controlled trial primarily designed to provide preliminary evidence of efficacy aerobic-based exercise training program on cognitive and everyday function among older adults with mild sub-cortical ischaemic vascular cognitive impairment.

**Methods/Design:**

A proof-of-concept single-blinded randomized trial comparing a six-month, thrice-weekly, aerobic-based exercise training group with usual care on cognitive and everyday function. Seventy older adults who meet the diagnostic criteria for sub-cortical ischaemic vascular cognitive impairment as outlined by Erkinjuntti and colleagues will be recruited from a memory clinic of a metropolitan hospital. The aerobic-based exercise training will last for 6 months. Participants will be followed for an additional six months after the cessation of exercise training.

**Discussion:**

This research will be an important first step in quantifying the effect of an exercise intervention on cognitive and daily function among seniors with sub-cortical ischaemic vascular cognitive impairment, a recognized risk state for progression to dementia. Exercise has the potential to be an effective, inexpensive, and accessible intervention strategy with minimal adverse effects. Reducing the rate of cognitive decline among seniors with sub-cortical ischaemic vascular cognitive impairment could preserve independent functioning and health related quality of life in this population. This, in turn, could lead to reduced health care resource utilization costs and avoidance of early institutional care.

**Trial Registration:**

ClinicalTrials.gov Protocol Registration System: NCT01027858.

## Background

Cerebrovascular disease is the second most common etiology contributing to dementia in older adults [1-4] and may be the most under-diagnosed and yet most treatable form of cognitive dysfunction in older adults [5]. Vascular cognitive impairment is defined as the loss of cognitive function resulting from ischaemic, ischaemic-hypoxic, or hemorrhagic brain lesions as a result of cerebrovascular disease and cardiovascular pathologic changes. As vascular cognitive impairment is predominantly a sub-cortical frontal form of cognitive disorder with prominent executive dysfunction [6], it directly impairs everyday function [7], such as managing finances, transportation, or the telephone. Taken together, vascular cognitive impairment has the potential to severely impact the ability to function autonomously within society [8].

A number of epidemiological studies suggest that modification of vascular risk factors, such as hypertension, diabetes mellitus, and hypercholesterolemia may be helpful in slowing down the progression of vascular cognitive impairment [9-12]. Hence, one promising approach to delay the progression of vascular cognitive impairment is aerobic-based exercise training. Critically, evidence is mounting that exercise has benefits for cognitive function among seniors. Aerobic-based exercise training may be of specific benefit in slowing the progression of cognitive decline among seniors with vascular cognitive impairment by reducing key vascular risk factors associated with metabolic syndrome. Aerobic exercise may also act specifically on disease pathophysiology [13], for example, by improving capillarization or modulating brain neurotrophic factors [14-16], and may even decrease brain amyloid load in the brain [17]. Finally, aerobic-based exercise training as an intervention strategy for individuals with vascular cognitive impairment is attractive as it could be delivered at a population-level.

The growing consensus is that small vessel diseases have an important role in vascular cognitive impairment [18,19]. Small vessel disease often presents as undetected "covert" strokes in the sub-cortical white matter. Compared to other forms of vascular cognitive impairment, the sub-cortical ischaemic vascular disease sub-type is a more homogenous form of the disease with a more predictable outcome [20]. While mild **S**ub-cortical **I**schaemic **V**ascular **C**ognitive **I**mpairment (SIVCI) describes those individuals whose symptoms are not associated with substantial functional impairment [18], persons with mild SIVCI have a high risk of progression to dementia [18,21]. Seniors with mild SIVCI are also at risk for executive dysfunction [18], and subsequently at risk for decline in everyday function (i.e., ability to perform instrumental activities of daily living [ADLs]) [7]. Instrumental ADLs refer to capacities that are required for autonomous function within society [8]; the ability to perform instrumental ADLs is a key aspect of functional independence and health related quality of life [8]. Thus, persons with mild SIVCI represent an ideal target population for intervention strategies, as preservation of their cognitive and functional status will likely maintain and prolong their ability to live independently and with quality. To our knowledge, no randomized controlled trial has assessed the effect of aerobic-based exercise training on cognitive and everyday function among seniors with mild SIVCI. Thus, we aim to carry out a proof-of-concept single-blinded randomized controlled trial primarily designed to provide preliminary evidence of efficacy of a six-month, thrice-weekly, aerobic-based exercise training program on cognitive and everyday function among older adults with mild SIVCI. In addition, this proof-of-concept study will aim to explore the effect of aerobic-based exercise training on: 1) serum glucose, hemoglobin A1c, and lipids; 2) inflammatory biomarkers; 3) physical function; 4) health related quality of life; and 5) health resource utilization. Finally, this study will demonstrate the feasibility of delivering the intervention in this population, determine the recruitment rate, determine the rate of withdrawal, and provide estimates of the variances, co-variances and effect sizes of the proposed outcome measures to inform the sample size for a larger definitive trial.

## Methods/Design

### Design Outline

We will conduct a six-month proof-of-concept single-blinded randomized trial and follow our study cohort for an additional six months of follow-up (see Figure 1).

**Figure 1 F1:**
[figure not shown]
**Overview of the flow of participants through the Promotion of the Mind Through Exercise (PROMoTE) Trial**.

### Recruitment

We will recruit seniors with mild SIVCI through the University of British Columbia Hospital Clinic for Alzheimer Disease and Related Disorders (UBCH-CARD). All individuals who receive care at the UBCH-CARD have the option to sign a consent form providing access to their records for research purposes and indicating their willingness to be approached for research studies. One trained research assistant will review the charts of patients at the UBCH-CARD who have expressed interests to participate in research studies. Clinicians at the UBCH-CARD will also be informed of this study and they will assist in recruitment by flagging the charts of their current patients who may qualify for this study to our research assistants. Those who appear eligible based on detailed chart review will be mailed an information package regarding the study, including the consent form.

For those who are interested in participating, a one hour consent and screening session will be arranged. Once informed consent is obtained, we will perform the screening tests. Those who remain eligible after the screening session and who later provide written recommendation from their physician indicating their appropriateness to participate in an aerobic-based exercise training program will proceed to baseline assessments.

### Eligibility

We will recruit individuals who fulfill the diagnostic criteria for SIVCI as outlined by Erkinjuntti and colleagues [22], which requires the presence of both cognitive syndrome (as defined in Section A below) and small vessel ischaemic disease (as defined in Section B below).

A. Cognitive Syndrome defined as:

1. *Dysexecutive Syndrome: *Some impairment in goal formulation, initiation, planning, organizing, sequencing, executing, set-shifting and maintenance, or abstracting.

2. *Memory Deficit: *Some impairment in recall in the presence of relatively intact recognition and benefit from cueing.

3. *Progression: *Deterioration of A1 and A2 from a previous higher level of functioning that are not per se interfering with complex occupational and social activities.

B. Small Vessel Ischaemic Disease defined as:

1. *Evidence of relevant cerebrovascular disease by brain imaging *(in the last 12 months) defined as the presence of both:

i. Periventricular and deep white matter lesions: Patchy areas of low attenuation (intermediate density between that of normal white matter and that of intraventricular cerebrospinal fluid) or diffuse symmetrical areas of low attenuation with ill defined margins extending to the centrum semiovale, plus at least one lacunar infarct (correlating to the white matter grading scale greater than 3 from the Cardiovascular Health Study) [23,24]; and

ii. Absence of cortical and/or cortico-sub-cortical non-lacunar territorial infarcts and watershed infarcts, haemorrhages indicating large vessel disease, signs of normal pressure hydrocephalus, or other specific causes of white matter lesions (e.g., multiple sclerosis, leukodystrophies, sarcoidosis, brain irradiation, etc).

2. *Presence or a history of neurological signs *as evidence for cerebrovascular disease such as lower facial weakness, Babinski sign, sensory deficit, dysarthria, gait disorder, or extrapyramidal signs consistent with sub-cortical brain lesion(s).

In addition, individuals must meet the following inclusion criteria: 1) Montreal Cognitive Assessment (MoCA) [25] score less than 26 at screening; 2) Mini-Mental State Examination (MMSE) [26] score of ≥ 20 at screening; 3) Community-dwelling; 4) Live in Metro Vancouver; 5) Have a caregiver, family member, or friend who interacts with him/her on a weekly basis; 6) Able to comply with scheduled visits, treatment plan, and other trial procedures; 7) Must be able to read, write, and speak English in which psychometric tests are provided with acceptable visual and auditory acuity; 8) Stable on a fixed dose of cognitive medications (e.g., donepezil, galantamine, rivastigmine, memantine, etc.) that is not expected to change during the 12-month study period, or, if they are not on any of these medications, they are not expected to start them during the 12-month study period; 9) Provide a personally signed and dated informed consent document indicating that the individual (or a legally acceptable representative) has been informed of all pertinent aspects of the trial. In addition, an assent form will be provided at baseline and again at regular intervals; 10) Able to walk independently; and 11) Must be in sufficient health to participate in the study's aerobic-based exercise training program. This will be based on medical history, vital signs, physical examination by study physicians, and written recommendation by family physician indicating one's appropriateness to participate in an aerobic-based exercise training program.

The exclusion criteria are: 1) Absence of relevant small vessel ischaemic lesions on an existing brain computed tomography (CT) or magnetic resonance imaging (MRI); 2) Diagnosed with another type of neurodegenerative (e.g. AD) or neurological condition (e.g., multiple sclerosis, Parkinson's disease, etc.) that affects cognition and mobility; 3) At high risk for cardiac complications during exercise and/or unable to self-regulate activity or to understand recommended activity level (i.e., Class C of the American Heart Risk Stratification Criteria); 4) Have clinically significant peripheral neuropathy or severe musculoskeletal or joint disease that impairs mobility; 5) Taking medications that may negatively affect cognitive function, such as anticholinergics, including agents with pronounced anticholinergic properties (e.g., amitriptyline), major tranquilizers (typical and atypical antipsychotics), and anticonvulsants (e.g., gabapentin, valproic acid, etc.); or 6) Planning to participate, or already enrolled in, a clinical drug trial concurrent to this study.

Ethical approval has been obtained from the Vancouver Coastal Health Research Institute (V07-01160) and the University of British Columbia's Clinical Research Ethics Board (H07-01160).

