#### Descriptors

Using a wall mounted stadiometer, standing height will be measured as stretch stature to the 0.1 cm per standard protocol. Weight will be measured twice to the 0.1 kg on a calibrated digital scale. General health and socioeconomic status will be ascertained by a questionnaire. Participants will undergo a clinical assessment with neurologist and study physicians ([name] and PL) at baseline to confirm current health status and eligibility for study, including clinical impressions of overall cognitive and functional status. The Neuropsychiatric Inventory (NPI), an informant-rated instrument, will be used to evaluate behavioural and neuropsychiatric symptoms [32].

Physical activity, not including the study-assigned exercise classes, will be determined by the valid and reliable Physical Activities Scale for the Elderly (PASE) questionnaire [33,34]. Designed for those aged 65 years and older, participants use a 12-item scale to self-report the average number of hours per day spent participating in leisure, household, and occupational physical activities over the previous seven-day period. Accounting for extracurricular physical activities throughout the randomized trial is essential to ascertain the specific effects of the delivered interventions on cognition and function.

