#### Usual Care (CON) Group

Participants in the CON group will receive educational material about vascular cognitive impairment and about stress management, healthful diet, and smoking. However, this group will not receive specific information regarding physical activity. Participants in the AT group will also be offered these educational materials.

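### The co-enrolment exclusion covers only drug trials, so people in another exercise or cognition-targeted trial are eligible: a minor, potential risk to the contrast that one line would remove

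*Protocol article*

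**What the plan says.** The sixth exclusion criterion in the Eligibility section of the protocol article reads "Planning to participate, or already enrolled in, a clinical drug trial concurrent to this study". None of the other inclusion or exclusion criteria mentions another trial. The nearest is an inclusion criterion on general compliance, "Able to comply with scheduled visits, treatment plan, and other trial procedures", which does not rule out a second behavioural trial.

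Under Recruitment, a research assistant will "review the charts of patients at the UBCH-CARD who have expressed interests to participate in research studies". The clinic's consent form gives access to records and covers patients "indicating their willingness to be approached for research studies".

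The Usual Care section says that controls receive educational material, but that "this group will not receive specific information regarding physical activity". It sets no limit on outside exercise or cognitive training.

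The Descriptors section deals with outside activity: "Physical activity, not including the study-assigned exercise classes, will be determined by the valid and reliable Physical Activities Scale for the Elderly" (PASE). It gives the reason: "Accounting for extracurricular physical activities throughout the randomized trial is essential to ascertain the specific effects of the delivered interventions on cognition and function".

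**The concern.** The trial tests a behavioural intervention, and its three primary endpoints are cognitive and functional (ADAS-Cog, EXIT-25, ADCS-ADL). The co-intervention most likely to overlap with that contrast is another exercise or cognition-targeted programme, yet the co-enrolment rule names only drug trials.

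The rule also sits oddly beside the rest of the article. Drug co-interventions are closely controlled: cognitive medication must be stable for the 12 months, and drugs that may impair cognition are excluded. Controls are deliberately given no information on physical activity, and accounting for outside activity is called essential. A person exercising in another trial nevertheless passes the stated criteria.

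What could be at stake is the size of the AT versus CON difference. Participants know their allocation, and a control who trains in another study stays in the comparator. The Statistical Analyses section restricts AT to those attending 60% of sessions but states no matching rule for CON. The trial's effect sizes and variances are also meant to inform the sample size of a definitive trial, so a diluted estimate would carry forward.

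**Working it through.** The point rests on wording, so the passages are compared first. The arithmetic after that only shows what would have to be true for the gap to matter.

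**1. Scope of the rule.**
- Barred by the sixth exclusion: a current or planned concurrent drug trial.
- Not barred by any stated criterion: a current or planned trial of exercise, cognitive training or another non-drug intervention aimed at cognition or activity.
- Partial cover elsewhere: PASE asks about leisure, household and occupational activity over the previous seven days. It would pick up outside exercise, but it has no place for cognitive training. It measures activity and does not prevent co-enrolment.
- Analysis: the stated model is an analysis of covariance with the baseline measurement. Neither PASE nor co-enrolment is named in it.

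**2. Direction of any effect.** Let d be the true AT effect, e the benefit of an outside programme, a the share of AT and c the share of CON who obtain it. If benefits add,

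observed contrast = d + (a − c) × e.

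- With a = c the contrast stays at d, and the outside benefit mainly adds variance.
- With c > a the contrast shrinks towards zero.

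Dilution therefore needs differential uptake, or an outside benefit that does not add to the trial's own.

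**3. The plan's own power figure.** The Sample Size section gives an effect size of 0.60, 30 per group, alpha 0.05 (sidedness not stated) and power of 0.75 to 0.80. By the normal approximation, power = Φ(d × √(30/2) − z), with 0.60 × √15 = 2.324.
- One-sided: Φ(2.324 − 1.645) = 0.751, which matches the lower end.
- Two-sided: Φ(2.324 − 1.960) = 0.642, which does not match.

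The upper end is reached one-sided at 35 per group (0.807), not at 30. Sidedness is a separate matter, so both versions are carried below.

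**4. A conditional illustration.** The article gives no value for a, c or e. Take the unfavourable case a = 0 and e = d, so that the effect is 0.60 × (1 − c).

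| c (assumed) | effect | power, one-sided | power, two-sided |
|---|---|---|---|
| 0 | 0.60 | 0.751 | 0.642 |
| 1 of 30 | 0.58 | 0.726 | 0.613 |
| 5% | 0.57 | 0.713 | 0.598 |
| 10% | 0.54 | 0.672 | 0.552 |
| 20% | 0.48 | 0.585 | 0.460 |

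Here c is the share of controls who gain the full benefit, not the share who co-enrol. If the other trial were itself randomised 1:1 against an inactive control, about half of those co-enrolled would be treated. Then c = 10% would need about 20% of controls co-enrolled, or 6 of 30, with no counterpart in AT. The table shows sensitivity to an assumption. It does not estimate what will happen.

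**5. Effect of the fix on stated figures.** None: 30 evaluable and 35 recruited per group, 70 in total, are unchanged.

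**The case against.** The strongest reply is that nothing here is false or self-contradictory. The article condenses a fuller protocol, and undertakings not to join other studies often sit there or in consent forms. That reply stands against one stronger reading. A reader might infer that nothing prevents a participant from entering another trial after randomisation. The article's silence on conduct during follow-up does not establish that. The reply does not remove the point about the entry rule, because that rule is stated and its scope is explicit.

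A reader might also infer that contamination is likely because recruitment draws on research-willing patients. The Recruitment section records only access to charts and willingness to be approached. It does not say that competing trials exist or that patients join more than one study. That unblinded controls would seek a programme elsewhere is conjecture.

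A third tempting inference is that co-enrolment would make the primary comparisons uninterpretable. The documents do not support that either. Similar uptake mainly adds noise, and excess uptake among controls attenuates the effect, which is conservative for a claim of efficacy. The comparator is usual care, which does not promise inactivity. PASE covers the exercise side in part, and how it enters the analysis may properly be left to an analysis plan that is not shown.

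Finally, a narrower entry rule has a price in a small single-clinic trial for which recruitment rate is itself an outcome. That is fair, and it argues for naming the barred trials precisely.

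**Conclusion.** The concern holds as a limited point: the stated co-enrolment exclusion is narrower than the trial's own contrast needs. A person in, or planning to join, another exercise or cognition-targeted intervention trial meets the criteria as written.

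The consequence is conditional. Dilution requires that such enrolment occurs, that it delivers a benefit on the trial's endpoints, and that controls take it up more than AT participants or that the benefits do not add. The documents give no rate for any of these. Under the unfavourable assumptions in the working, 10% of controls gaining the full effect elsewhere would cost about 8 points of power one-sided (0.751 to 0.672) or 9 points two-sided (0.642 to 0.552). If nobody co-enrols, the cost is zero. Neither figure should be quoted as an expected loss.

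Cheap improvement; severity low.

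**What to change.** Extend the sixth exclusion along these lines: *current or planned enrolment, from screening through the 12-month visit, in a drug trial or in any interventional trial of exercise, cognitive training or another intervention aimed at cognition or physical activity; observational studies are allowed.* At the existing 6- and 12-month visits, ask about enrolment in other studies and tabulate any by arm.

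The cost is one line in the eligibility criteria and one question at two visits already planned. The downside is that a few otherwise eligible volunteers may be lost from a single-clinic pool. Naming the types of trial keeps that loss small and reduces the judgement needed at screening.

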### Sample Size

Prior to launching a definitive randomized controlled trial, it is essential that the feasibility of conducting such a trial be demonstrated. A sample for a definitive study with multiple end-points and outcome variables will require several hundred participants and warrant a multi-site study. Given that no study has examined the effect of exercise on cognitive function in SIVCI, we have selected a sample size of 30 participants per group. Studies have suggested a standard deviation of change of 6 to 7 [27-29] in Alzheimer Disease Assessment Scale Cognitive (ADAS-Cog) scores among individuals with vascular cognitive impairment. We highlight that a recent exercise trial among seniors at risk for AD with ADAS-Cog as the primary outcome measure demonstrated an effect size of 0.60 [30]. Thus, assuming an alpha of 0.05, 30 participants per group will provide a power of 0.75 to 0.80. We estimate a drop-out rate of 10% during a 12-month period. Hence, we are aiming to recruit 35 participants per group (i.e., 70 participants in total) which will accommodate a conservative 15% drop-out rate.

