### Statistical Analyses

As a primary objective of this study is to provide preliminary evidence of **efficacy **we will compare participants of the AT group who are compliant with the intervention (defined as attending 60% of the total exercise sessions) to the CON group rather than using an intention-to-treat analysis as would be appropriate in a pivotal clinical trial. In addition, no adjustment for multiple endpoints will be made since in a proof-of-concept study a Type II error is of more concern than a Type I error [52]. For each of the three primary endpoints (i.e., ADAS-Cog, EXIT-25, ADCS-ADL), the change from baseline to six months and 12 months will be assessed using an analysis of covariance model incorporating the baseline measurement. Observing a statistically significant difference on **any **of the three primary outcomes will be considered preliminary evidence of efficacy.

We will also report variances, co-variances, and effect sizes, as well as sampling feasibility (i.e., ease of recruitment, recruitment rate, withdrawal rate). This information will inform sampling for future trials.

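### The stated power of 0.75 to 0.80 does not follow from the effect size, alpha and group size printed beside it; it depends on sidedness or a covariate gain that is not stated

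*Protocol article*

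**What the plan says.** The power statement is in the Sample Size section of the protocol article. It rests on these inputs:

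- Variability: "Studies have suggested a standard deviation of change of 6 to 7 [27-29" points on ADAS-Cog.
- Effect: an earlier exercise trial in people at risk for Alzheimer disease, also with ADAS-Cog as primary outcome, which "demonstrated an effect size of 0.60 [30".
- Level: "assuming an alpha of 0.05", with no mention of one or two sides.
- Conclusion, introduced as following from the above: "assuming an alpha of 0.05, 30 participants per group will provide a power of 0.75 to 0.80".

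The section then raises recruitment to 35 per group to allow for 15% drop-out. It gives no target difference in points and no baseline correlation.

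The Statistical Analyses section plans an analysis of covariance with the baseline value for each of the three primary endpoints. Its success rule names no direction: "Observing a statistically significant difference on" any "of the three primary outcomes will be considered preliminary evidence of efficacy". It waives adjustment for multiple endpoints on the ground that a Type II error is the greater worry at this stage.

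**The concern.** The text presents the power as a consequence of the effect size, alpha and group size, so a reader should be able to reproduce it from them. Under the ordinary reading of an unqualified 5% level, the result falls 12 to 17 percentage points short of the stated range.

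This is the only power figure in the article, and the trial puts Type II error first when it waives multiplicity adjustment. If the tests are two-sided and unadjusted, the chance of missing a true ADAS-Cog effect of 0.60 is about 37% (1 − 0.63), against the 20% to 25% that the text implies. Anyone who weighs a non-significant ADAS-Cog result, or sizes the later definitive trial, needs to know which figure applies.

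**Working it through.** **Inputs.** From Sample Size: standardised effect d = 0.60, n = 30 per group (35 recruited), alpha = 0.05. From Randomization: 1:1 allocation. Sidedness is not stated, so both cases are shown.

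**Method.** Two-sample t-test, noncentral t with noncentrality d × √(n/2) and 2n − 2 degrees of freedom. The normal approximation is shown for comparison.

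**Step 1: trying to reproduce the stated range.**

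At n = 30 the noncentrality is 0.60 × √15 = 2.324, with 58 degrees of freedom. At n = 35 it is 0.60 × √17.5 = 2.510, with 68 degrees of freedom.

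| n per group | Two-sided, t (normal) | One-sided, t (normal) |
|---|---|---|
| 30 | 0.628 (0.642) | 0.743 (0.751) |
| 35 | 0.697 (0.709) | 0.800 (0.807) |

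The lower end, 0.75, is met at 30 per group only by a one-sided test, to rounding. The upper end, 0.80, is not met at 30 per group by either unadjusted test. It appears one-sided at 35, which is the number before drop-out. The drop-out allowance itself is consistent: 35 × 0.85 = 29.75, about 30.

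**Step 2: what the stated range would require, two-sided.**

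- At 30 per group, power 0.75 needs d = 0.69 and power 0.80 needs d = 0.74.
- At d = 0.60, power 0.75 needs 40 evaluable per group and power 0.80 needs 45.
- In points, d = 0.60 is 0.60 × 6 = 3.6 to 0.60 × 7 = 4.2. An effect of 0.74 is 0.74 × 6 = 4.4 to 0.74 × 7 = 5.2.

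**Step 3: does the SD range of 6 to 7 explain the power range?** Once the effect is standardised, the SD drops out. If a fixed point difference had been used instead, one that gives two-sided power 0.75 at SD 7 would give about 0.87 at SD 6. That range is wider than the stated one.

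**Step 4: does the analysis of covariance explain it?** Let r be the correlation between baseline and follow-up, with equal variances at both times.

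- If 0.60 is in units of the SD of change, the effective d is 0.60 / √((1 + r)/2). Then r = 0.5 gives d = 0.693 and two-sided power 0.75; r = 0.3 gives d = 0.744 and power 0.81; r = 0.8 gives d = 0.632 and power 0.67.
- If 0.60 is in units of the raw-score SD, the effective d is 0.60 / √(1 − r²). Then r = 0.50 gives d = 0.693 and power 0.75; r = 0.58 gives d = 0.737 and power 0.80; r = 0.70 gives d = 0.840 and power 0.89.

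Two-sided 0.75 to 0.80 at 30 per group is therefore attainable, with r from about 0.5 down to 0.3 on the first scale or about 0.50 to 0.58 on the second. A one-sided covariance analysis could also reach 0.80 at 30 per group, for example with r = 0.7 on the change scale (d = 0.651, power 0.80). Each route needs an input that the section does not give.

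**The case against.** The strongest reply is that the article never says the test is two-sided. A one-sided 5% test is a recognised choice for proof-of-concept work, and it gives the lower stated figure at 30 per group and the upper one at 35. This stands: a reader may infer that the power is simply 0.63 and the Type II error simply 37%, and the document does not support that without the two-sided, unadjusted assumption. An unqualified 0.05 and a success rule that names no direction point towards two sides, but they do not settle it.

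Second, the planned analysis is a covariance model, and the article does not say which SD standardises the 0.60. On the raw-score scale a moderate correlation is enough to give two-sided power of 0.75 to 0.80. This also stands as a possibility. The neighbouring sentence on the SD of change favours the other scale, where a higher correlation brings less gain, but it does not prove it. A condensed article may leave the correlation to the full protocol. Even so, the printed sentence derives the power from the printed inputs and mentions no covariate gain.

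Third, this is a proof-of-concept trial. The stated reason for 30 per group is that no earlier study exists in this population, and success may come on any of three endpoints, so ADAS-Cog power is not the trial's overall chance of a positive result. At the expected 10% drop-out, about 31 to 32 per group would remain (35 × 0.90 = 31.5). All of this limits the consequence. A reader might also infer that a null result will be taken as evidence against exercise, but nothing in the document says it would be read that way.

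None of these points makes the sentence correct as printed.

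**Conclusion.** The point holds in a conditional form. From an effect size of 0.60, alpha 0.05 and 30 per group, an unadjusted test has power of about 0.63 (two-sided) or 0.74 (one-sided), and the full range of 0.75 to 0.80 comes from neither. The range would be right only with a covariate gain, or with a one-sided test whose upper figure is taken at 35 per group. The article declares no one-sided test and claims no covariate gain.

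The figures assume that exactly 30 per group are analysed and that the 0.60 is a standardised difference between groups. The covariance figures also assume equal variances at baseline and follow-up. The error is a misstated power figure that should be corrected; it does not invalidate the design or the sample size of a proof-of-concept trial.

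**What to change.** Keep the sample size. In the Sample Size section, state whether the test is one- or two-sided, which SD standardises the 0.60, and whether any gain from the baseline covariate is assumed. Then restate the power to match one of these:

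- **Two-sided, unadjusted:** with 30 evaluable per group and an effect size of 0.60 (3.6 to 4.2 ADAS-Cog points at SD 6 to 7), power is about 0.63; power of 0.80 needs an effect size of about 0.74.
- **One-sided 0.05, unadjusted:** power is about 0.74 at 30 per group. Declare the one-sided test in both the Sample Size and the Statistical Analyses sections.
- **With covariate gain:** state the correlation, its source and the resulting power.

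The cost is a sentence or two and no extra participants. The downside is that the stated power becomes less favourable unless a covariate gain can be justified.
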